## Process evaluation

In line with the Medical Research Council guidelines [46] an embedded process evaluation will be undertaken. This will use documentary analysis, non-participant observation and semi-structured interviews to explore and understand the implementation of the intervention, and how it is experienced and understood by providers and recipients.

In addition to main trial participation, trial recruits and their carers will be asked to optionally consent to potential participation in the process evaluation. A purposeful sample of consented individuals will be approached across ten trial sites throughout the intervention delivery phase of the trial. Purposive sampling is planned for all types of data collection associated with the process evaluation. The intention is to sample participants with different levels of frailty, level of intervention, gender and age. We will also sample, through observations, intervention delivery at different time points, including first and last visits by therapists or therapy assistants. Trial intervention therapists and therapy service managers will also be approached to consent to their potential involvement in process evaluation activities. Sampling for therapists will seek to include different levels of qualification and years of experience, different gender as well as different sites and regions. Where possible we will sample therapists who have completed intervention delivery to a minimum of three participants.

Consented carers will be approached for process evaluation involvement in line with the participant purposeful sample. Usual care participants will be sampled similarly and invited for interview. Purposive sampling will also be undertaken as part of the documentary analysis in order to ensure records are reviewed from a range of different therapists and participants.

Researchers undertaking the process evaluation will:
Observe and monitor intervention therapist training, and their engagement with training.Engage in informal discussion with therapy teams in early and late stages of intervention delivery to understand how organisational and professional contexts impact on rehabilitation provision to the participant group.Interview therapy service managers to establish what constitutes usual care across trial sites.Observe home-based delivery of the HOPE programme in a sample of participants across participating sites and across participants with a range of degrees of frailty. Observations will include the interactions between therapists, participants and family members/carers (where present), and note contextual factors potentially influencing programme delivery, receipt and enactment.Interview a purposive sample of intervention delivery staff.Interview a purposive sample of intervention participants (including those who did and did not engage with the intervention). Carers will also be invited to participate in the semi-structured interviews where it is apparent they have some involvement in supporting participants with the intervention, and/or usual care.Interview a purposive sample of trial participants allocated to usual care arm of the trial. This will establish whether they participated in other programmes post discharge provided by the NHS, social care, voluntary or private sector, which may have included similar structured exercise provision, and whether this was evident in particular regions or sites.Evaluate intervention adherence using data from participant exercise diaries and therapy records.

Normalisation Process Theory (NPT) will provide the framework for process evaluation [47]. Quantitative and qualitative data to evaluate intervention fidelity will be analysed using descriptive statistics, and content analysis. Field notes and interview data will be analysed using a thematic approach [48].

## Oversight and monitoring

### Composition of the coordinating centre and trial steering committee {5d}

Study oversight will be provided by the independent Trial Steering Committee (TSC), who will meet every 6 months. This comprises of four professionals within a research field involving our study population, with expertise in our trial methodology (statistics, health economics, process evaluation, rehabilitation trials and elderly medicine). The TSC also include two lay personnel who will bring knowledge and expertise from the study population and service user perspective.

The trial management group (TMG) will include the chief investigator and grant co-applicants, CTRU trial management personnel, AUASR trial management and process evaluation teams, and Academic Unit of Health Economics personnel at both the University of Leeds and the University of Exeter. The TMG will also include two lay personnel who will bring knowledge and expertise from the study population and their carers’ perspective. The TMG meetings will be scheduled on a quarterly basis as a minimum, but monthly in the initial phase of trial setup; responsibilities include the set-up and promotion of the trial, on-going monitoring and management of the trial and interpretation and dissemination of results.

### Composition of the data monitoring committee, its role and reporting structure {21a}

For a study of this nature, a separate Data Monitoring Committee is not required. Rather the TSC will adopt a safety monitoring role, with a sub-committee to review safety issues where necessary.

Safety data (deaths and hospitalisation resulting from falls and/or fractures), collected at 5 and 11 months per participant, will be reported by arm to each TMG and TSC meeting and escalated as appropriate. An annual safety report is produced for REC. As deaths are expected within the study population they will not be subject to expedited reporting to the REC, unless the TSC advises otherwise.

### Adverse event reporting and harms {22}

Adverse Events will be reported by sites if classified as related or unexpected (related to the study intervention). Trial sites will be trained in the timely reporting procedures for Suspected and Unexpected Serious Adverse Reactions/Events. Expected Adverse Events data will be reported by trial sites at 5 and 11 months per participant (including death, and hospitalisation rates due to falls and/or fracture). Participants are asked regarding falls and fracture incidence at 6- and 12-month follow-up. We do not specifically ask participants to describe other experienced harms, other than via opportunities to observe and discuss adherence related issues via the process evaluation activity. Safety data as described above will be reported by arm in the final trial report.

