#### Participant identification and eligibility

Participant recruitment will vary by site dependent upon service infrastructure and usual NHS rehabilitation patient pathways. These will be established during site set-up and strategies will be put in place to maximise identification and recruitment of potential patients. Patients will be screened on admission to the relevant ward/service by local research staff. Those meeting the following eligibility criteria will be identified through discussions with ward staff:
Age ≥65 years.Admitted to general medicine/elderly medicine or trauma and orthopaedics care following acute illness or injury then discharged home from hospital or from IC.Have mild, moderate or severe frailty, defined as a score of five to seven on the nine-item Clinical Frailty Scale (CFS).Ability to complete the Timed Up and Go Test (TUGT) without additional external support.Ability to give informed consent to participate in the study.

The following patients will be excluded:
Permanent care home residents.Those with significant cognitive impairment at baseline (defined as Montreal Cognitive Assessment (MoCA) test < 20).Recent (< 3 months pre-randomisation) myocardial infarction, or unstable angina.Very severe frailty (defined as score of eight on CFS).Terminally ill (defined as score of nine on CFS).Receiving palliative care.Referral at discharge for condition-specific rehabilitation (e.g. pulmonary rehabilitation, stroke rehabilitation, falls prevention programme).Another household member in the study.Currently participating in the HERO trial or another contraindicated study.

Documented reasons for ineligibility or declining participation will be closely monitored by the Research team as part of a regular review of recruitment progress, to allow for generalisation of study results in accordance with CONSORT reporting guidelines, and to highlight any issues in the identification or recruitment of patients during the internal pilot.

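### Adverse events other than deaths, falls and fractures are reported only if judged intervention-related, so that part of the by-arm safety report cannot show excess risk

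*Protocol article*

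**What the plan says.** The section on adverse event reporting and harms {22} sets up separate reporting routes.

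- **Route 1, by relatedness:** "Adverse Events will be reported by sites if classified as related or unexpected (related to the study intervention".
- **Route 2, expected events:** "Expected Adverse Events data will be reported by trial sites at 5 and 11 months per participant (including death, and hospitalisation rates due to falls"; the list then also names fractures. No relatedness condition and no limit to one arm is attached. The data collection section {18a} confirms that sites are asked for these data on each participant.
- **Participant report:** "Participants are asked regarding falls and fracture incidence at 6- and 12-month follow-up". For anything else, "We do not specifically ask participants to describe other experienced harms, other than via opportunities to observe and discuss adherence related issues" arise in the process evaluation.
- **Presentation:** "Safety data as described above will be reported by arm in the final trial report".

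The section on the data monitoring committee {21a} describes what goes to the trial management group and steering committee: "Safety data (deaths and hospitalisation resulting from falls and/or fractures), collected at 5 and 11 months per participant, will be reported by arm". Elsewhere, the plan takes readmission, mortality and fall hospitalisation from HES and linked ONS data (Outcomes {12}). It compares readmission, mortality, new care home placement and fall-related attendance or admission between arms (Statistical methods {20a}).

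**The concern.** Route 1 makes reporting depend on an attribution that can hardly be made for someone who was not given the intervention. Tabulated by arm, it sets a count filtered by attribution to HOPE against a count that is almost empty by design. The difference between the two columns does not measure excess risk over usual care.

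Detection is also likely to differ. Intervention participants are seen and telephoned by therapists who know the allocation and keep therapy records. Site researchers receive randomisation confirmation without the allocation {16c}, and data collectors are blind {17a}. Judgements of relatedness will therefore probably start with the therapists, and the article describes no equivalent regular contact for controls.

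What is at stake is the harms conclusion for a progressive exercise programme in frail older people. For causes other than falls, fractures and death, the article names no comparison between the arms. The primary analysis is not affected.

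**Working it through.** **1. Arm sizes.** The point has no figure of its own, but the illustrations use the arm sizes in Sample size {14}, so these were reproduced first. Inputs: difference 3, SD 9.47, two-sided 5%, 90% power, 35% loss, mean cluster size 7, ICC 0.03, CV of cluster size 0.7.

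- Two-sample t-test: 211 per arm.
- Design effect, intervention arm only: 1 + [(0.7² + 1) × 7 − 1] × 0.03 = 1.283.
- Control: 211 / 0.65 = 324.6, so 325. Intervention: 211 × 1.283 / 0.65 = 416.4, so 417. Total 742, as stated.

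**2. What each source captures.**

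| Source | Events | Depends on relatedness? | Alike in both arms? |
|---|---|---|---|
| Route 1, site reports {22} | Other adverse events | Yes | No |
| Route 2, sites at 5 and 11 months {18a, 22} | Death, fall/fracture hospitalisation | No | Yes |
| Participant questionnaires, 6 and 12 months {12, 22} | Falls, broken bones | No | Yes |
| HES/ONS {12} | Readmission without stated cause, fall hospitalisation, death | No | Yes |

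Only route 1 could show another specific cause of harm, and only route 1 is lopsided.

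**3. Size of the distortion in route 1 (assumed rates; the article gives none).** Let a proportion r of each arm have some other serious event, and let a proportion q of the intervention-arm events be judged related.

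- True counts: 325r and 417r. For r = 10% to 30%: 32.5 to 97.5 in control, 41.7 to 125.1 in intervention.
- Reported counts: about 0 in control and 417rq in intervention. For q = 2% to 10%: 417 × 0.10 × 0.02 = 0.8, up to 417 × 0.30 × 0.10 = 12.5.

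The true risks here are identical in the two arms, yet the table would show about 0 against 1 to 13.

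**4. Does readmission without stated cause fill the gap?** The standard error of a risk difference is √[p₁(1−p₁)/325 + p₂(1−p₂)/417], with no allowance for clustering and complete HES linkage assumed.

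- Assumed readmission risk of 50% in both arms: √(0.25/325 + 0.25/417) = 3.7 points. An excess of 3 points is 3/3.7 = 0.8 standard errors.
- The same 3-point excess in one cause, assumed 4% against 7%: √(0.0384/325 + 0.0651/417) = 1.66 points. The excess is 3/1.66 = 1.8 standard errors, with a 95% interval of about −0.2 to 6.2 points.

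A cause-specific table is the more sensitive of the two, and opposing changes in other admissions cannot cancel the signal. It is still not a powered test: the chance of excluding zero is about P(Z > 1.96 − 1.81) = 44%. Because the arms are unequal, risks should be compared, not counts. At 4% in both arms the expected counts would already be 13 and 17.

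**The case against.** **Much of the safety data is symmetric.** A reader of route 1 alone might infer that usual care has almost no reportable events at all. The documents do not support this: deaths and fall/fracture hospitalisations are collected for every participant, both arms report falls and fractures, and readmission and care home placement are compared. This stands, and it confines the point to other causes.

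**The by-arm sentence may not cover route 1.** Section {21a} uses safety data to mean deaths and fall/fracture hospitalisations, and {22} could be read the same way. The plan also says reported by arm, not tested. But the sentence in {22} refers to everything described above it, and that includes route 1. If the narrower meaning was intended, one line should say so.

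**The route 1 wording is ambiguous, and the article condenses a fuller protocol.** It is unclear whether an unexpected but unrelated event is reportable; the parenthesis suggests not. The expected-event list is introduced as an inclusion, so it may not be exhaustive, although {18a} and {21a} name no other event. Ambiguity also calls for correction.

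**A control could have a related event.** The plan anticipates contamination ({16c} and the discussion of intervention training). So the control count is near zero, not necessarily zero, and a report limited to the intervention arm would lose such events.

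**Tabulation of HES diagnoses may be in the analysis plan.** That plan is not shown, so it cannot be said that HES will go unused for this purpose. The finding rests on the reporting rule and the stated decision not to ask about other harms, and not on that silence.

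**Conclusion.** The point holds in a limited form. For adverse events other than deaths, falls and fractures, the stated rule makes site reporting depend on attribution to the intervention. That part of the by-arm report is near zero in usual care by construction and cannot estimate excess risk. The sources that are alike in both arms cover deaths, falls, fractures and readmission without stated cause; no other cause-specific harm is named for comparison.

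Three stronger inferences are not supported:

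- **That the table must make HOPE look worse.** Under-attribution could equally give a reassuringly low count.
- **That the plan identifies a cardiac risk.** It excludes recent "myocardial infarction, or unstable angina", but states no such concern about the exercise programme.
- **That the numerical illustrations are forecasts.** Every event rate in them is assumed; only the arm sizes come from the plan.

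The change is worth making because the harms conclusion depends on it and the cost is low.

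**What to change.** Amend {22} in two respects.

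1. **Relatedness-based events.** Present them descriptively, state that they are not a between-arm comparison, and list any control-arm event arising from contamination. Clarify whether unexpected but unrelated events are reportable.
2. **Between-arm harms summary.** Base it on sources identical for both arms: deaths from ONS, and HES emergency admissions from randomisation to 12 months grouped by primary diagnosis (at least cardiovascular; fall, fracture or injury; other). Give risk differences with 95% intervals, labelled as descriptive estimates and not powered tests.

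**Cost.** Wording changes and one further table. HES and linked ONS data are already to be requested in a single download at the end of follow-up {18a}. Fall hospitalisations are to come from the same source, so some cause coding is already needed; that the extract holds primary diagnosis and admission type should be confirmed. No new participant contact is required.

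**Downside.** Cause groups depend on hospital coding, events that do not lead to admission stay uncaptured, and intervals for rare causes will be wide.

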### Frequency and plans for auditing trial conduct {23}

Researchers will notify the CTRU if there is a breach of protocol or Good Clinical Practice principles likely to significantly affect participants’ safety, health and wellbeing, or scientific value of the research.

The CTRU/Sponsor reserve the right to conduct intermittent source data verification on a sample of participants. Source data verification will involve direct access to patient notes at the participating hospitals, and other relevant investigation reports.

### Plans for communicating important protocol amendments to relevant parties (e.g. trial participants, ethical committees) {25}

Protocol amendments will be processed in line with HRA and REC guidelines and processes. Sites and investigators will be notified and agreement/capacity to implement sought.

### Dissemination plans {31a}

The NIHR Yorkshire and Humber Applied Research Collaboration (ARC) Research Implementation Advisory Group (RIAG) will be approached to discuss the trial results and potential dissemination of outputs.

Representatives of NHS England and Public Health England will be on the RIAG, along with NHS and local authority commissioners and providers, facilitating widespread dissemination. We will also involve the National ARC Healthy Ageing, Frailty and Dementia collaboration to disseminate findings nationally.

If the HOPE programme is found to be effective, we intend to develop an implementation pack for commissioners to support implementation. We will also make our intervention materials freely available, including the intervention manual, training package and supporting documentation, if effectiveness is demonstrated. Alongside journal publication, we will also aim to present at conferences nationally and internationally. Profession-specific circulations/forums will also be utilised to disseminate results. The clinical/research teams at trial sites will be provided with a trial results summary. We intend to produce an output specifically for the trial participants and their families, summarising the trial findings in a lay publication for circulation. This will be supplemented with information on our web site and social media.

## Discussion

### Screening processes

Feasibility discussions, setting-up and starting recruitment at trial sites, demonstrate that all trial sites are different in terms of service provision and pathways through the acute hospital, to intermediate care services. The foci of screening and recruitment activity differ between organisations, but a challenge facing all research teams is the numerous pathways from admission to ultimate rehabilitation discharge, and the variability and unpredictable duration of patients’ time under the care of those services. Screening and recruitment is challenging when split across many services and settings between both hospital services and separate bed-based and community-based rehabilitation services. Local research teams’ screening and tracking processes for potential participants are likely to evolve over time as services evolve and pathways potentially change.

### Intervention training

To maximise HOPE programme intervention fidelity, a therapist training package will be delivered to all interventional therapists. Intervention training will include clinical reasoning for the HOPE programme exercises, behaviour change strategies and practical delivery of the programme. Research principles including the importance of avoiding contamination via providing intervention principles to control participants will also be discussed. Supervision of therapy staff will be by usual NHS line management. Details of training provision, including content, attendance, duration, and training providers will be documented. Intervention therapists will have access to training materials to support intervention delivery.

Therapists will be provided with ongoing trial-specific training updates via teleconferences and newsletters. Training refresher sessions will be available for therapists where a gap in intervention provision has occurred, or upon request. New therapists joining the team due to rotations/turnover will be provided with the same training package. Any significant intervention training updates will be communicated directly with all therapists individually via email. The central trial team manager (physiotherapist) will seek site intervention team review meetings and feedback in the early stages of site opening.

### Potential impact of the HERO trial

This trial seeks to determine if the HOPE programme as extended rehabilitation for older people with frailty following acute illness or injury can improve physical health-related quality of life. The HOPE programme will be embedded within existing NHS services and pathways in a wide range of trusts both in terms of geography and size, and the diversity of the populations, to make the trial findings generalisable to a population of older people with frailty. The trial is powered such that robust conclusions may be drawn around clinical and cost-effectiveness of a theory-driven exercise intervention with potential for improved health-related quality of life. The results will improve awareness of the rehabilitation needs of older people with frailty. Findings from the embedded process evaluation will contribute to understanding factors which would facilitate wider implementation of the HOPE programme, these include factors influencing trial implementation, intervention fidelity, and the experiences and perspectives of trial participants and providers. The HERO trial findings will have considerable potential for benefit to older people with frailty and for health and social care services, through the commissioning and delivery of evidence-based rehabilitation services, if effectiveness is demonstrated.

## Trial status

Protocol v5.0 27/01/2020. Recruitment began December 2017 and is expected to conclude August 2021.

## Abbreviations

A&E: Accident and Emergency
ARC: Applied Research Collaboration
AUASR: Academic Unit for Ageing and Stroke Research
CFS: Clinical Frailty Scale
CTRU: Clinical Trial Research Unit
DGH: District General Hospital
DMC: Data Monitoring Committee
EQ5D-5 L: EuroQol 5 Domains 5 Levels
GP: General practice
HERO: Home-based Extended Rehabilitation for Older people
HES: Hospital Episode Statistics
HOPE: Home-based Older People’s Exercise
HRA: Health Research Authority
IC: Intermediate care
ICC: Interclass correlation coefficient
ICER: Incremental cost-effectiveness ratio
ID: Identification
ISRCTN: International Standard Randomised Controlled Trials Number
ITT: Intention to treat
MAR: Missing at random
MCS: Mental health Component Summary (of SF36)
MNAR: Missing not at random
MoCA: Montreal Cognitive Assessment
NEADL: Nottingham Extended Activities of Daily Living
NHS: National Health Service
NPT: Normative Process Theory
ONS: Office for National Statistics
PCS: Physical health Component Summary (of SF36)
PI: Principle Investigator
PIS: Patient information sheet
PSSRU: Personal Social Service Research Unit
QALY: Quality-adjusted life year
RCT: Randomised controlled trial
REC: Research Ethics Committee
RIAG: Research Implementation Advisory Group
SF36: Modified Short Form 36 item health questionnaire
SPIRIT: Standard Protocol Items: Recommendations for Interventional Trials
TMG: Trial Management Group
TSC: Trial Steering Committee
TUGT: Timed Up and Go Test
